### Primary outcome and intervention

This is a mixed-methods behavioural study integrating quantitative and qualitative data to investigate primary and secondary endpoints. The purpose of the intervention is to determine the effect that personal activity trackers have on physical activity as measured by exercise capacity on 6-min walk test post ACS. The personal activity monitor will be provided to participating patients based on their allocation to the intervention group and agreement to participate in cardiac rehabilitation. Patients in the intervention group will download the Fitbit smart phone application, and the devices will be paired in a face-to-face education session. Patients will also receive education on its use, along with assistance in programming exercise targets as per recommended guidelines.

Each participant in the intervention arm will be registered with a cloud storage service via an allocated, de-identified, password protected email address and will be instructed to wear the device during all waking hours. The study will take place over 8 weeks commencing at the time of their discharge from hospital.

### Exercise prescription

Patients in both groups will be encouraged to exercise as per guideline recommendations [17] over the course of the study period. Patients in the intervention arm will be encouraged to meet a target of at least 10,000 steps per day, with the device programmed to this goal. In men who underwent an exercise rehabilitation program, improvement in walking distance (i.e. steps per day) was a strong independent predictor of survival, and a useful guide to prognosis [36] The study coordinators will be able to view these de-identified step counts in real time, however there will be no further interaction with patients in either group until the 8-week follow-up review.

The routine community cardiac rehabilitation program that all will be encouraged to attend encourages patients to engage in regular moderate intensity exercise increasing in a graded degree over a seven-week period centred around a walking program. Moderate intensity is described as exercise that is ‘neither too hard, nor too easy’, with ‘mild shortness of breath, sweating and increased heart rate’ as per the National Australian Heart Foundation recommendations [37].

### Tracking of cardiovascular risk factors

Prior to discharge from hospital patient cardiovascular risk factors will be collected. Blood pressure, cholesterol levels, blood glucose levels, HbA1c, weight, smoking status, waist circumference and BMI will be assessed and recorded along with survey responses as outlined below. Patients will be provided with specific education and given written information as to recommended target levels and strategies to achieve them as per standard of care. There will be no additional blood tests required during the index admission as these parameters represent the standard of care at our institution.

### Screening assessments

Patients will undergo full comprehensive assessment at baseline prior to hospital discharge. This, including all questionnaires, will all be repeated at the 8-week follow-up appointment.

Exercise Capacity – Improvement in exercise capacity (i.e. walking ability) will be assessed via the six-minute walking test (6MWT) in a standardized fashion by trained assessors [33]. Walking distance and walking speed have been demonstrated to be inversely related to cardiovascular events, survival and hospitalisation in patients with cardiovascular disease [38–40].

Physical Activity – The International Physical Activity Questionnaire (Short) [41] will be used to determine physical activity status. Patients will be considered physically inactive if they do not meet the current guideline recommendation for physical activity.

Blood Pressure & Heart Rate – Blood pressure will be measured using an automated sphygmomanometer with pulse oxymetry to measure resting heart rate after a five-minute period of seated rest. Blood pressure will be repeated three times, as per guideline recommendations, with the first measurement discarded and the average taken of the second and third [42].

Blood Tests – Fasting lipids, blood glucose and HbA1c results will be available from inpatient notes. This will be taken as the baseline recording and repeated through the same hospital lab at 8 weeks.

BMI & Other Risk Factors – Body mass index will be derived from the weight (kg) divided by the height (m) squared. Waist circumference, at the level of the umbilicus, will be measured using an anthropometric tape. Smoking status will be recorded, defined as either current, ex-smoker, or lifelong non-smoker with number of pack years recorded where indicated. One pack year will be defined as 20 cigarettes a day, for one year.

Depression - Assessment for depression will be undertaken with the Cardiac Depression Scale – Short Form (CDS-SF) [43].

Exercise Motivation and Quality of Life: QOL assessment will be undertaken via the Short-Form Health Survey Questionnaire (SF-36) [44]. Exercise Motivation will be assessed via the Exercise Motivation Inventory 2 (EMI-2) questionnaire [45].

### Dietary habits

In the intervention group, patients will be encouraged to complete a food diary through the Fitbit smartphone application. This feature allows patients to enter food amounts, time of consumption and gives a running calorie count of both calories consumed and calories expended based on personal anthropometric data entered into the application (I.e. age, height, weight) and activity levels. Patients in the control arm will also be encouraged to keep a similar food diary. Both groups will receive dietary education through cardiac rehabilitation program attendance.

### Cardiovascular health education

All patients will undergo regular cardiac rehabilitation sessions as run by the health service. This incorporates an extensive teaching program around cardiovascular health education, risk factor modification, exercise prescription and dietary advice along with the implications of psychological stress on cardiovascular disease. This program is run in a group setting with family members invited to attend. It is available at various times throughout the week to facilitate high attendance rates. It is run over either a 6-week period incorporating weekly daytime sessions or over 4 weeks incorporating longer evening sessions to facilitate patients with work commitments.

### Cardiac medication list

Patient medications on discharge and at the end of the study will be recorded, with self-reported reasons documented for any alterations.

### Safety considerations

Overall this is a low risk study. Studies have shown patients with pre-existing heart disease have an event rate of one in every 62,000 h of exercise with those without heart disease having a risk of a cardiac event between 1 in 400,000–800,000 h of exercise [46]. Some studies have suggested that strenuous activity is associated with increased risk of cardiac death or complications [47]. However, recent data suggests that near maximal intensity exercise in patients in the week of and thereafter following an uncomplicated acute coronary syndrome is safe [48, 49].

To minimize any risk to patients, those who have a significantly increased risk of suffering harm from this intervention have been excluded from the study. Should any participant experience or report any adverse events or symptoms at any time during the study period they will be advised on how to manage these symptoms and then to seek medical evaluation initially via their general practitioner or emergency department. Patients will be requested to contact the principal investigator about any reported adverse events or symptoms and these will be promptly recorded and managed.

### Standard care

Regardless of treatment assigned all patients will receive the same standard of care post their acute coronary syndromes. This includes specialist cardiology inpatient management, hospital based education, pre-discharge planning, discharge documentation forwarded to their general practitioner, referral to cardiac rehabilitation, a chest pain action plan and cardiologist follow-up organized 4–6 weeks post index event.

### Statistical analysis

The intervention arm will be compared against the control arm on an intention to treat analysis basis. All statistical analyses will be performed using SPSS v23 (IBM, USA). Baseline characteristics will be summarized using descriptive statistics. Paired Student-t test will be used for all normally distributed continuous variables and will be described as mean with standard deviation. Variables not normally distributed will be analysed using the Wilcoxon Signed Rank test. Categorical variables will be described as frequencies and percentages and will be compared using a Pearson chi-squared test.

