### Outcome assessment

#### Primary outcome

The primary outcome is a change in six-minute walk distance that will be measured in a standardized fashion as per the American Thoracic Society Statement 2002 [33]. The initial test will be undertaken during index hospital admission with telemetry monitoring and will be repeated at eight weeks as an outpatient. It will be undertaken by a trained assessor.

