#### Secondary outcomes

All secondary outcomes will be measured at baseline and at 8-week follow-up. Table 1 summarizes the secondary outcomes of our study. In addition to those already mentioned, a number of self-reported indices will be recorded at follow-up appointment. Namely, smoking status, date participants returned to work (if applicable), medication adherence, and cardiac rehabilitation attendance and completion, defined as attending all sessions. Any major adverse cardiovascular events (MACE) will be recorded. MACE is defined as the composite of death, non-fatal myocardial infarction, stroke and unplanned revascularization. In addition, cardiac related hospital admissions will also be documented. Both primary and secondary outcomes are outlined in Table 1.

**Table 1 Tab1:** Primary and Secondary endpoints

Primary Outcome
• Six-minute walk test distance
Secondary Outcome
• Fasting Lipid Levels
• Fasting Glucose
• Resting Blood Pressure
• Resting Heart Rate
• Weight and Body Mass Index (BMI)
• Waist Circumference
• Smoking Status (self-Reported)
• Attendance and adherence to Cardiac Rehabilitation
• Depression/Mood Assessment
• Compliance with Secondary Prevention Pharmacotherapy
• Exercise Motivation (EMI-2)
• Quality of Life

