### Sample size required

We calculated that 152 participants (76 in both the intervention and control groups) would need to be enrolled for the study to have a statistical power of 80% to detect a clinically important increase of 25 m in the six-minute walk test [21, 22], in the intervention group as compared with the control group, with a two-sided alpha level of 0.05. Accounting for 20% loss to follow-up a minimum of 92 patients in each arm will be required. If the power was to increase to 90% at 5% level of significance 101 patients would be required in each arm of the study. We plan to recruit 100 patients in each arm, totalling 200 patients.

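### The paired tests named for continuous outcomes neither compare the arms nor use patients without a week-8 walk, so they do not deliver the stated between-arm intention-to-treat analysis

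*Protocol article*

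**What the plan says.** All places are in the protocol article.

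- **Statistical analysis** sets the comparison: "The intervention arm will be compared against the control arm on an intention to treat analysis basis".
- The same section names the tests for continuous data: "Paired Student-t test will be used for all normally distributed continuous variables and will be described as mean with standard deviation", and "Variables not normally distributed will be analysed using the Wilcoxon Signed Rank test". It names no two-sample test or model for a continuous outcome. Only categorical variables get a test that can compare groups (Pearson chi-squared).
- **Primary outcome** defines the endpoint: "The primary outcome is a change in six-minute walk distance". There are two measurements and none between them: "The initial test will be undertaken during index hospital admission with telemetry monitoring and will be repeated at eight weeks as an outpatient".
- **Sample size required** is built on a difference between arms: "We calculated that 152 participants (76 in both the intervention and control groups) would need to be enrolled", for 80% power to detect 25 m at two-sided 0.05. It then allows for missing outcomes: "Accounting for 20% loss to follow-up a minimum of 92 patients in each arm will be required". Planned enrolment is 100 per arm.

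**The concern.** The section states one question and names tests for another. A paired t-test or signed rank test on six-minute walk distance asks whether patients changed between admission and week 8. The primary hypothesis asks whether tracker patients changed more than control patients.

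All patients are recovering from an acute coronary syndrome and are offered the same rehabilitation, so improvement in both arms is plausible whatever the tracker does. Two within-arm tests, one significant and one not, would not be a test of the difference. A single paired test on all patients would ignore allocation.

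The same tests use complete pairs only. A patient who does not return for the second walk has no pair and drops out, although an intention-to-treat comparison of the randomised arms is promised. If return rates or reasons differ by arm, the difference among returners need not equal the difference among all randomised. Participants know their allocation, so differential return is possible, though nothing in the article shows it.

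**Working it through.** **1. The sample size presupposes a two-sample comparison.** No SD is stated, so I solve for it.

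- From 76 per arm, 80% power: SD = 25 / [(1.96 + 0.8416) × √(2/76)] = 55.0 m.
- From 101 per arm, 90% power: SD = 25 / [(1.96 + 1.2816) × √(2/101)] = 54.8 m.

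The two figures agree with each other under a two-sample formula. Because the SD was solved for, this does not validate the SD. It does show that the design calculation fits a between-arm test, which the analysis section does not name.

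The figure of 92 is 76 × 1.2 = 91.2, rounded up. Dividing by the expected retention gives 76 / 0.8 = 95. This has no consequence at the planned 100 per arm.

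**2. What the named test would detect.** Assume that 55 m is the SD of the change score and that 80 per arm complete.

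- Within one arm, SE = 55 / √80 = 6.15 m, so a mean improvement of 1.96 × 6.15 = 12.1 m is significant with no control arm involved.
- Between arms, SE = 55 × √(2/80) = 8.70 m, and the target is a difference of 25 m.

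These are different hypotheses with different standard errors.

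**3. Who is used.** A 20% loss from 200 is 40 patients, leaving 160 (80 per arm). Power of a two-sample test for 25 m at SD 55 m:

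| Scored per arm | Power |
|---|---|
| 100 (no loss) | 89.5% |
| 80 (20% loss from 100) | 82.0% |
| 73.6 (20% loss from 92) | 78.7% |

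At the planned enrolment, power stays above 80%.

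**4. Possible bias (illustration; inputs assumed).** Let lost patients change by D metres less than completers, and let f be the fraction lost in an arm. The completers' difference is then off by D × (f_tracker − f_control). Take 20% overall loss split 25%/15%, so SE = 55 × √(1/75 + 1/85) = 8.71 m.

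| D (m) | Bias if 25% tracker, 15% control | Type I error | Bias if split reversed | Power at 25 m |
|---|---|---|---|---|
| 20 | +2 m | 5.6% | −2 m | 75% |
| 40 | +4 m | 7.4% | −4 m | 67% |
| 60 | +6 m | 10.6% | −6 m | 59% |

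With equal loss this bias is zero. A separate gap arises if the tracker effect differs in those lost. With 20% lost in each arm and 25 m in completers, the all-randomised difference is 0.8 × 25 + 0.2 × e, where e is the effect in those lost:

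- e = 25 m gives 25 m;
- e = 12.5 m gives 22.5 m;
- e = 0 gives 20 m.

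The loss split, D and e are not in the article.

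**The case against.** **The article is silent on missing data, and silence is not an error.** This stands. Rules for a missing walk, death or inability to walk are commonly left to the full protocol or analysis plan, which are not shown. A reader might infer that the trial will run a completers' analysis mislabelled as intention to treat. The article does not say so. It defines no completer set and excludes nobody, and an imputation rule elsewhere would be compatible with analysing patients in their assigned arm. A missing change score is unobserved, but it can still be modelled.

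**Paired tests are not what drops the incomplete patients.** This also stands. A two-sample t-test on change, or an ANCOVA without imputation, would drop the same patients. Changing the test therefore settles the between-arm question only, and the result still needs an accurate label.

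**The authors may have meant the paired tests for within-arm change only.** That is possible, but the text assigns them to all continuous variables and names nothing else that could compare the arms on a continuous outcome. The mismatch lies in what is stated.

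**Those lost need not be the sickest.** A reader might infer that they are, because the recorded events include death and stroke: "MACE is defined as the composite of death, non-fatal myocardial infarction, stroke and unplanned revascularization". The article gives no event rate over 8 weeks and no reasons for loss. It excludes several high-risk groups, and an infarction or revascularisation need not prevent a walk test. The 20% is also a planning allowance, not a forecast.

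**Conclusion.** The point holds as a mismatch between the stated comparison and the named tests. Followed as written, the tests do not compare the arms, even with complete data, and they use only patients with both walks. The first part needs no assumption. The second rests on the endpoint having two measurements and on nothing being added elsewhere for missing ones.

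If loss reaches the 20% allowance, 40 of 200 patients would not contribute. The cost in power at 100 per arm is moderate (89.5% to 82.0%, at the back-calculated SD of 55 m). The size and direction of any bias cannot be derived from the article. The 2 to 6 m and 5.6% to 10.6% figures show what the assumed loss splits would do and are not predictions.

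**What to change.** In Statistical analysis, replace the paired tests for the primary outcome with a between-arm comparison of week-8 six-minute walk distance adjusted for baseline distance (ANCOVA), analysing patients in their randomised arm. The baseline walk is already collected before randomisation. Paired summaries can stay as description within arms.

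Then do one of two things about missing week-8 walks:

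- impute them from variables known for lost patients: baseline walk, age, the physical activity questionnaire (IPAQ) and the baseline depression score (CDS-SF). Self-reported rehabilitation attendance cannot serve, because it is recorded at the visit these patients miss; or
- describe the result as an analysis of patients with both walks.

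In either case, add a simple sensitivity analysis in which lost patients are made progressively worse, separately by arm. Settle this before outcomes are seen.

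The cost is a change of wording and slightly more analysis work. No extra patients or measurements are needed.

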## Methods/Design

UP-STEP ACS is a prospective single-blinded, two-arm, parallel, randomized control trial with an aim to enrol 200 patients (100 in each arm). The study design is displayed in Fig. 1. This protocol is prepared based on the SPIRIT 2013 statement [32].

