### Randomization

Once all screening assessments are completed and eligibility is confirmed patients (*n* = 200) will be randomized in a 1:1 fashion to receiving the personal activity monitor (Fitbit Charge 2) in addition to usual cardiac rehabilitation or the usual cardiac rehabilitation alone through a computer based randomization process (Fig. 1). A computer-generated table will allocate patients in fixed blocks of four. In order to prevent selection bias, the allocation sequence will be concealed from the investigators enrolling and assessing patients utilizing computer randomization software.

Baseline patient demographics and pre-defined screening and assessment, including the 6-min walk test, will occur prior to randomization after patients have given informed consent. Assessors of the primary outcomes will be blinded to the treatment allocation, however participants are not able to be blinded.

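### The only tests named for continuous outcomes, including the primary, are paired tests; no named test makes the between-arm comparison that the hypothesis and sample size call for

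*Protocol article*

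**What the plan says.** The Statistical analysis section opens with the intended comparison: "The intervention arm will be compared against the control arm on an intention to treat analysis basis". It then names the tests. For continuous data: "Paired Student-t test will be used for all normally distributed continuous variables". For the rest: "Variables not normally distributed will be analysed using the Wilcoxon Signed Rank test". Categorical variables "will be compared using a Pearson chi-squared test". No other test is named in the article.

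The other sections fix what has to be tested:

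- **Primary outcome:** "The primary outcome is a change in six-minute walk distance", from the index admission to eight weeks. This is a continuous variable.
- **Hypotheses:** the tracker is expected to improve exercise capacity relative to standard care.
- **Sample size required:** a 25 m increase "in the intervention group as compared with the control group, with a two-sided alpha level of 0.05", with 76 per arm for 80% power and 101 per arm for 90%.
- **Methods/Design:** two parallel randomised arms, 100 patients in each.
- **Randomization:** 1:1, and "A computer-generated table will allocate patients in fixed blocks of four". No matching of patients across arms is described.

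**The concern.** A paired t-test or signed rank test needs two linked measurements per unit. Here the only linked measurements are a patient's own baseline and week-8 values. The named tests can therefore ask whether one arm changed. They cannot ask whether the arms changed by different amounts, which is the trial's question.

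This matters more than usual because of the timing. The baseline walk is done in hospital, on telemetry, during the acute event. Both arms then receive the same standard care, and cardiac rehabilitation built around a graded walking program. Improvement in both arms is plausible with no tracker effect at all. A significant before-after test in the tracker arm, or significance in that arm but not in the control arm, could then be taken for a tracker effect. The same rule covers the continuous secondary outcomes, such as lipids, glucose, blood pressure, weight, waist circumference, mood and quality of life.

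**Working it through.** **1. Which named test could compare the arms on walk distance?**

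| Named test | Variables assigned | Compares independent arms? |
|---|---|---|
| Paired t | all normally distributed continuous | no |
| Wilcoxon signed rank | continuous, not normal | no |
| Pearson chi-squared | categorical | yes, but not for a continuous outcome |

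Blocks of four balance the numbers per arm; they do not create matched pairs. The opening sentence of the section states a between-arm comparison, and the tests that follow cannot carry it out for any continuous outcome.

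**2. The plan's own sample size.** The article gives no SD, so it has to be back-solved. The two-sample normal formula is n per arm = 2 × (SD × (z₀.₉₇₅ + z_power) / 25)². The z sums are 2.802 (80% power) and 3.242 (90% power).

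- At SD 54.8 m: 2 × (54.8 × 2.802 / 25)² = 75.4, so 76; and 2 × (54.8 × 3.242 / 25)² = 101.0, so 101. Both stated figures are returned.
- The one-sample (paired) formula drops the factor 2. At SD 77.5 m: (77.5 × 2.802 / 25)² = 75.4, so 76; and (77.5 × 3.242 / 25)² = 101.0, so 101. Both stated figures are returned again.

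The numbers alone therefore do not show which formula was used. The evidence that the trial was sized for a between-arm test is the wording of Sample size required.

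**3. What within-arm tests could do when the tracker has no effect.** Assumptions:

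- SD of change 54.5 m, close to the two-sample back-solved value;
- 80 completers per arm, that is, 100 less the 20% loss stated under Sample size required;
- the same true mean change m in both arms.

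The standard error of the mean change is 54.5/√80 = 6.09 m. The paired t statistic is noncentral t with 79 degrees of freedom and noncentrality m/6.09, and the two-sided 5% critical value is 1.99. Let p be the probability that one arm is significant. The arms are independent, so the probability that the tracker arm is significant and the control arm is not is p(1 − p).

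| Common improvement m | Tracker arm significant, p | Tracker arm only, p(1 − p) |
|---|---|---|
| 10 m | 36.8% | 23.2% |
| 12 m | 49.4% | 25.0% |
| 15 m | 68.1% | 21.7% |
| 20 m | 90.0% | 9.0% |
| 25 m | 98.2% | 1.8% |

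A valid two-sided 5% test between arms would favour the tracker in 2.5% of such trials, whatever m is.

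**4. Cost of correcting the test.** With an independent-samples comparison of change at SD 54.8 m, normal-approximation power for 25 m is 80.3% at 76 per arm and 82.3% at 80 per arm. The planned 200 patients therefore still suit the corrected test.

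**The case against.** The strongest defence is that the opening sentence of the Statistical analysis section, the Hypotheses and the Sample size section all state a between-arm comparison, and that a full analysis plan may exist and specify it. The intent is indeed clear, so a reader who infers that the primary hypothesis will never be tested goes too far. What stands is narrower: no named test addresses it. This is not detail left for later. The article assigns a test to all normally distributed continuous variables, and that test does not fit the design. A later plan would have to contradict it. Nor does the text confine the paired tests to within-arm description.

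Four further inferences are tempting and not supported:

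- **That the tracker would be declared effective on recovery alone.** The protocol gives no rule that significance in one arm counts as success. The table shows a risk, not a planned decision.
- **That the error rate is high whichever rule is used.** Under the tracker-arm-only rule it peaks near 12 m of common improvement, and by 25 m it is 1.8%, below 2.5%.
- **That 76 and 101 per arm can come only from a two-sample formula.** A one-sample formula at an SD of about 77.5 m returns them too.
- **That the absence of a baseline covariate is itself an error.** An unpaired test of change would answer the hypothesis validly; adjustment is an improvement. There is likewise no basis for requiring a hospital term, since Randomization describes no stratification by hospital.

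**Conclusion.** The point holds, and it must be fixed. As written, the article names only paired tests for every continuous outcome, including the primary. In an unmatched two-arm parallel trial, these cannot test the between-arm difference that the Hypotheses, the sample size and the section's own first sentence require. This conclusion follows from the text and needs no assumption.

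The size of the risk is illustrative only, because the article gives neither the SD of change nor the expected recovery. Under the assumptions above, with no tracker effect and 10 to 25 m of common improvement, the tracker-arm paired test is significant in about 37% to 98% of trials. Significance in the tracker arm only occurs in about 25% of trials at most and 2% at 25 m.

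**What to change.** Replace the sentences on continuous variables with one prespecified between-arm primary analysis that does not depend on a normality check. Suggested wording:

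*Week-8 six-minute walk distance will be compared between randomised arms by ANCOVA, with arm as factor and baseline distance as covariate, reporting the adjusted mean difference with its 95% confidence interval. Continuous secondary outcomes will be analysed in the same way. Where a rank test is wanted, the Mann-Whitney test will be used. Paired tests will be used only to describe change within each arm.*

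An independent-samples t-test of change would also cure the error. ANCOVA is preferred because baseline distance is already collected before randomisation.

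The cost is one reworded paragraph. No extra data or patients are needed, the sample size stands, and SPSS, the package already named, fits the model.
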